### Project Population

This study targets a population at risk of osteoarthritis. The risk of knee osteoarthritis after knee joint injury is up to 5-fold that of noninjured patients. As many as 50% of individuals with an anterior cruciate ligament (ACL) or meniscus tear develop knee osteoarthritis [21]. Therefore, to represent the whole distribution of osteoarthritis stages in the study sample, participants will be recruited from the clinic’s Meniscus/ACL/Cartilage (MAC) surgery registry at 2- and 5-year postoperative times. All patients from the MAC registry will be screened regardless of whether they have undergone isolated meniscal tear repair, isolated ligament reconstruction, or a combined meniscal and ligament procedure. Additionally, a healthy control group and a late-stage osteoarthritis group will also be included. The inclusion and exclusion criteria presented in Textbox 1, follow established standards and are consistent with those used in similar studies (eg, NCT02937064).

The total study sample will be 120 patients in 6 groups:

Group A: 20 healthy participantsGroup B1: 20 patients from the MAC registry at 2 years postoperative with normal outcomes (normal and poor outcomes are defined in section Recruitment)Group B2: 20 patients from the MAC registry at 2 years postoperative with poor outcomesGroup C1: 20 patients from the MAC registry at 5 years postoperative with normal outcomesGroup C2: 20 patients from the MAC registry at 5 years postoperative with poor outcomesGroup D: 20 patients booked for in-house unilateral TKA surgery for severe osteoarthritis

Even if it is not possible to perform an exact power analysis for the ML models to be trained, we can use a simple proxy model to estimate the effect size that we can reasonably expect to detect with a sample size of 120. Thus, if we aim to estimate the differences in KL gradings from the AEs, the smallest detectable correlation with 80% power and a significance level of *P*=.05 would be 0.25. In one-way ANOVA, this corresponds to a minimum explained variance of approximately 7%, which is considered a small-to-medium effect size [22]. Smaller effect sizes are unlikely to be detected within our population.

Textbox 1.Detailed inclusion and exclusion criteria for the groups.

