### Feature Analysis and Multivariate Modeling

In this stage we will study the association between the extracted parameters and osteoarthritis (using the KL or MOAKS grading as the dependent variable), both individually for each feature and also by creating linear and nonlinear multivariate models. For this, we will follow a strategy guided by the principles of (1) increasing complexity and (2) clinical explainability. Thus, the initial models we consider are linear discriminant analysis and logistic regression, which would be ideal options in case we have a reduced number of highly informative and discriminative features. In this ideal scenario, the models would be highly interpretable and easily translatable to a clinical description. In case more sophisticated models are required, we prioritize ensembles of decision trees, such as random forest and gradient boosting, due to the possibility of performing advanced feature importance analysis and derivation of statistical decision rules.

All features will be tested for normality by Shapiro-Wilk tests and presented as mean (SD; normally distributed data) or median and range and, if needed, in histograms, box plots, or violin plots (nonnormal data).

Associations between AE parameters and osteoarthritis (KL or MOAKS grading) will be evaluated using Pearson (normally distributed data) or Spearman (nonnormal data) repeated measures correlation coefficients, as well as with logistic regression models. Mixed ANOVA will be used to compare differences in the AE, osteoarthritis grading parameters between groups. Also, we will specifically assess the relevance of potential confounding variables such as BMI, age, activity level, and gender. The significance level will be set to *P*=.05, and due to the potentially large number of tests, we will apply the Holm post-hoc correction to all *P* values. For multivariate models, the statistical association will be characterized using leave-one-subject-out nested cross-validation, with a subsequent estimation of a confidence interval for prediction accuracy. This is the most conservative and robust cross-validation strategy for overfitting , and with our sample size (n=120), we will have a good estimation of the model variance. Statistical analyses will be done with R (version 4; R Foundation), Matlab (version 2021b or higher; MathWorks, Inc), and Python (version 3.6 or higher; Python Software Foundation).

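### The 7% explained variance given for one-way ANOVA is only the two-group conversion of r=0.25; the six study groups need about 10% and five KL grades about 9%, before the planned Holm correction

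*Protocol article*

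**What the plan says.** Project Population first concedes that the machine-learning models cannot be powered exactly and then says: "we can use a simple proxy model to estimate the effect size". The basis is 120 participants, and the result is given as "80% power and a significance level of *P*=.05 would be 0.25" for the correlation between acoustic emissions and KL grading. The next sentence carries this over to analysis of variance: "In one-way ANOVA, this corresponds to a minimum explained variance of approximately 7%, which is considered a small-to-medium effect size". The paragraph ends: "Smaller effect sizes are unlikely to be detected within our population". No number of ANOVA groups is named there.

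The same section sets out the design: "The total study sample will be 120 patients in 6 groups", with 20 in each. EOS Radiography defines KL as grades 0 to 4, so five levels.

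Feature Analysis and Multivariate Modeling plans a mixed ANOVA to compare the groups. On multiplicity it says: "due to the potentially large number of tests, we will apply the Holm post-hoc correction to all" P values.

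**The concern.** The variance that a one-way ANOVA can detect depends on the number of groups. A correlation coefficient uses one degree of freedom and fixes no such number. A figure derived from r=0.25 therefore cannot be printed as the ANOVA threshold of a six-group study without recalculation. The significance level is a second mismatch: the threshold is worked out at .05 for one test, while the plan adjusts every P value.

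This is the article's only quantitative statement of what 120 participants can show. If the true thresholds are higher, a reader who meets a non-significant acoustic feature may conclude that an effect of 7% or r=0.25 has been made unlikely, when the analysis would often have missed it.

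**Working it through.** **Inputs.** N=120, power 80%, significance level .05, and six groups of 20 (all from Project Population); five KL grades (EOS Radiography). Sidedness is not stated; two-sided reproduces the printed value. The number of tests under Holm is not given, so 20 and 100 are assumptions used to show a range.

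**1. The article's correlation.** By Fisher's z, the smallest detectable r is tanh[(z for α/2 + z for power)/√(N−3)].
- (1.960 + 0.842)/√117 = 2.802/10.817 = 0.259, and tanh(0.259) = 0.253.
- Power at r=0.25 is Φ(0.2554 × 10.817 − 1.960) = Φ(0.803) = 79%.
- A one-sided test would give 0.226.

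The printed 0.25 is reproduced for one unadjusted two-sided test.

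**2. Where 7% comes from.** r² = 0.25² = 6.25%. The corresponding f² = r²/(1−r²) = 0.0625/0.9375 = 6.7%. Either rounds to the region of the printed figure, and both are one-degree-of-freedom conversions.

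**3. One-way ANOVA.** I used the noncentral F distribution with k−1 and N−k degrees of freedom and noncentrality λ = N·η²/(1−η²), one value per person, equal groups, unadjusted .05, solved for 80% power.

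| Groups k | Minimum η² | Power at η²=7% |
|---|---|---|
| 2 | 6.2% | 85% |
| 3 | 7.6% | 76% |
| 4 | 8.6% | 70% |
| 5 (KL grades) | 9.4% | 64% |
| 6 (study groups) | 10.1% | 60% |

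At 7%, λ = 120 × 0.07/0.93 = 9.03 whatever k is. For six groups 80% power needs λ = 120 × 0.1009/0.8991 = 13.5. Of the group numbers shown, only k=2 reaches 80% power at 7%. Detecting 7% across six groups would take about 177 participants; this only shows the size of the gap and is not a proposal to enlarge the study.

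**4. Effect of Holm, first step (α = .05/m), m assumed.**
- m=20: z for α/2 = 3.023, so r = tanh[(3.023 + 0.842)/10.817] = 0.34. Power at r=0.25 is 40%.
- m=100: z for α/2 = 3.481, so r = tanh[(3.481 + 0.842)/10.817] = 0.38. Power at r=0.25 is 24%.
- The six-group ANOVA at the same levels needs 16.5% and 19.5% explained variance.

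**The case against.** The strongest reply is that the figure is openly a proxy in an exploratory study. Relevance of the Project says 120 was chosen as feasible within the project's time limits, and Limitations already names sample size as a major weakness. No sample size, endpoint or decision rule rests on the 7%. This stands, and it is why the point is moderate. It does not make the conversion right for a one-way ANOVA.

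It can also be said that the sentence names no number of groups and concerns the relation of acoustic emissions to KL, for which a one-degree-of-freedom measure is natural. That defends r=0.25. But the text says one-way ANOVA, and the groupings the article offers have six or five levels.

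Third, the planned analysis is a mixed ANOVA with two knees and two visits per person, so 10.1% is itself an approximation. This is correct and must be said in any restatement. If 240 knees were independent, the six-group minimum would be 5.2%. Knees of one person are correlated, however, and the article bases its figure on 120.

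Fourth, the Holm figures depend on an assumed number of tests and on the strictest step; later steps are less strict. This also stands, so they serve as illustration only.

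A reader might go further and infer that the article promises to detect every effect above its threshold. It does not: it says only that smaller effects are unlikely to be found, and that remains true if the threshold rises. Nor is the small-to-medium label shown to be wrong, since it rests on a cited source that is not at hand.

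**Conclusion.** The point holds for the ANOVA figure and for the unadjusted significance level; r=0.25 itself is correct for a single unadjusted two-sided test. The printed 7% understates the minimum explained variance by about 3 percentage points for six groups (10.1%) and about 2.4 for five KL grades (9.4%). These values assume one value per person, equal groups and an unadjusted .05. With Holm the thresholds rise further, by an amount the document does not allow one to fix.

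It would be tempting to conclude that the study is too small or that its sample size was miscalculated. The document does not support that, because 120 was not derived from this calculation. What is overstated is the sensitivity reported to readers.

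**What to change.** In Project Population:
- State that r=0.25 (about 6% of variance) applies to one unadjusted two-sided test with one degree of freedom.
- Replace 7% with about 10% for the six study groups, or about 9% for five KL grades, described as a one-way approximation to the planned mixed ANOVA with one value per person.
- Add that under the planned Holm correction the detectable effect is larger, for example r of about 0.34 to 0.38 at the first step if 20 to 100 tests are assumed.

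The cost is a few sentences and a less favourable stated sensitivity. No participants, measurements or analyses change.

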**Inclusion criteria**
Group A:Aged 35-65 yearsPeople judge themselves to be of good subjective health without any knee problemsGroups B and C:Aged 35-65 yearsUnilateral knee surgery (other side as internal control)Participants in Meniscus/ACL/Cartilage (MAC) surgery registryCompleted patient-reported outcome measurements (PROM) questionnaires at 2 years or 5 years within the last 6 monthsGroup D:Aged 35-75 yearsPatient booked for total knee arthroplasty (TKA) due to severe osteoarthritis
**Exclusion criteria**
Inability to give consent or follow proceduresNo understanding of the German languageOpen wounds or tissue injuriesIrritated or infected sections on the limbsClass II obesity is defined by BMI ≥35 kg/m2 (comorbidities associated with obesity should be investigated in future studies)Uncooperative patients who disregard or cannot follow instructions, including those who abuse drugs and/or alcoholPregnant or with the intention to get pregnant (X-rays)Current address outside of SwitzerlandGroups B and C only: revision surgeries at the operated knee, death, known pathologies, or former injuries of the comparator knee

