**Methods:**

A total of 100 patients with previous reconstructive knee surgery and 20 healthy controls will be examined twice at a 9-month interval for both knees. Acoustic emissions (AE) will be recorded with the Inmodi knee brace (École Polytechnique Fédérale de Lausanne; EPFL) during 4 functional tests (unloaded flexion-extension, sit-to-stand test, one-step test, and walk test). Gold-standard osteoarthritis diagnostics will be assessed and evaluated by an experienced radiologist for (1) the magnetic resonance imaging (MRI) Osteoarthritis Knee Score (MOAKS) and (2) the Kellgren-Lawrence (KL) grading scores. Feature analysis and multivariate modeling will be used to study the association between the extracted sound parameters and osteoarthritis (MOAKS and KL). In addition, thermal images will be taken to investigate the state of inflammation. Participants will fill out 5 health-related questionnaires (Oxford Knee Score [OKS], Core Outcome Measures Index [COMI], University of California at Los Angeles [UCLA ]activity scale, Knee Injury and Osteoarthritis Outcome Score [KOOS], and Forgotten Joint Knee Score-12 [FJS-12]) at both time points.

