#### EOS Radiography

Long-leg radiographic images will be acquired in a standing position as stereoradiography using the EOS Edge (EOS X-Ray Imaging Acquisition System). The photon counting detector allows for a dose reduction by a factor between 8 and 10 compared to conventional X-ray radiography [24,25]. EOS imaging of the knee has been validated for osteoarthritis grading using KL grading scores [26].

For all participants, bilateral long-leg, standing EOS images in anteroposterior view will be retrieved and analyzed for:

Osteoarthritis grading (KL grade 0‐4)Compartmental joint space widthLeg alignment angles:Knee joint alignment (normal, varus, and valgus) measured with hip-knee-ankle angleMechanical axis lengthProximal tibia widthMechanical axis deviationJoint anglesMechanical lateral distal femoral angleMechanical medial proximal tibial angle

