#### AE Test With Inmodi Knee Brace

The tests will be done with the Inmodi knee brace (v2; Figure 1) for AE assessment of both knees simultaneously [18]. The brace is designed to not hinder movement and is made of biocompatible materials (polylactic acid/thermoplastic polyurethane) covered by silicon commonly used in orthopedics for direct skin contact. All the embedded electronics are fully isolated, without possible contact with the patient. The device consists of 2 parts to be attached on the limb with the help of straps (Figure 2):

The main part is to be positioned on the calf. This part has an embedded inertial measurement unit (IMU) module to collect kinematic data on the lower part of the limb and 2 microphones positioned in an enclosure covered by removable silicone. The microphones are placed at each extremity of a flexible arch to be positioned on the medial and lateral subpatellar regions. This mainframe also has a battery, microcontroller, and embedded flash memory to save the raw data.A secondary part to be positioned on the thighs and connected by USB to the main part. This secondary part has an IMU module to collect the kinematics of the upper part of the limb and an interface with buttons to start/stop the recording of all sensors.

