## Discussion

### Principal Findings

This exploratory study aims to identify biomarkers with a prognostic value in the prediction of osteoarthritis. Acoustic, kinematic, and thermal features will be extracted and combined with an artificial intelligence algorithm, and evaluated against gold-standard osteoarthritis diagnosis, such as radiographs and MRI. Some candidate acoustic biomarkers have been identified in a preliminary study [9], using a multifractal analysis method. However, multiple other candidates will be evaluated individually or in combination in our study. Therefore, the primary endpoint can be defined as the area under the curve of the receiver operating characteristic analysis of each biomarker or combination of biomarkers in the regression analysis, finally identifying the parameters with the highest sensitivity and specificity to predict early-stage osteoarthritis in clinical use. AE is patient-dependent, and as such, demographic and baseline health data will be captured and entered as covariates in the regression models. The secondary objective is to evaluate the value of these biomarkers in predicting osteoarthritis evolution. For this objective, the patients will be examined a second time at 9-month intervals, and the new biomarkers will be introduced in regression models to evaluate the predicted performance for osteoarthritis evolution.

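### More than half of the osteoarthritis-free knees will probably come from knees chosen for having no known problem, so AUC and specificity should also be reported within the operated knees before any claim about at-risk patients

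*Protocol article*

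**What the plan says.** The Abstract (Methods) states that participants "will be examined twice at a 9-month interval for both knees". The section on the knee brace test provides "for AE assessment of both knees simultaneously". Under EOS Radiography, "bilateral long-leg, standing EOS images in anteroposterior view will be retrieved" for Kellgren-Lawrence (KL) grading, and MRI Technique has both knees scanned for the MOAKS score. Every knee therefore has both a sound recording and a reference grade.

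Textbox 1 sets which knees enter. Group A members judge themselves free of knee problems. Groups B and C had surgery on one knee, the other serves as the within-person control, and the exclusion criteria remove patients with "known pathologies, or former injuries of the comparator knee". Group D is "20 patients booked for in-house unilateral TKA surgery for severe osteoarthritis".

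Project Population says: "This study targets a population at risk of osteoarthritis". It ties that risk to earlier knee injury: "As many as 50% of individuals with an anterior cruciate ligament (ACL) or meniscus tear develop knee osteoarthritis".

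Principal Findings says the primary endpoint can be defined as the AUC of each biomarker or combination, "finally identifying the parameters with the highest sensitivity and specificity to predict early-stage osteoarthritis in clinical use". Feature Analysis and Multivariate Modeling uses KL or MOAKS as the dependent variable and names BMI, age, activity level and gender as possible confounders. Neither section restricts the ROC analysis to one kind of knee or separates the results by kind.

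**The concern.** Specificity and AUC depend on which knees make up the osteoarthritis-free (OA-free) comparison. For a patient with earlier injury or surgery, the hard distinction is between a repaired knee with osteoarthritis and a repaired knee without it. In groups A to C, OA-free knees of the second kind can come only from the 80 operated knees. The other 120 knees were screened for having no known problem.

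The article's own premise, under Alternative Assessment Methods, is that abnormal sound comes from poor lubrication or surface damage. A repaired meniscus or cartilage surface could produce such sound without being graded as osteoarthritis. Two things are then at stake. False positives among operated knees would be diluted by untouched knees. And a parameter could rank high because it separates operated from untouched knees rather than osteoarthritic from non-osteoarthritic ones. Entering operated status as a covariate would not change which knees form the OA-free set.

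**Working it through.** The plan's only sizing figure, a detectable correlation of 0.25 with n = 120, reproduces (0.250 to 0.253, two-sided) but does not bear on this point. The check rests on the group sizes.

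**Knee count** (Project Population, Textbox 1). Six groups of 20 give the stated 120 participants, or 240 knees:
- Group A: 20 × 2 = 40 screened knees
- Groups B and C: 80 operated and 80 screened comparator knees
- Group D: 20 knees booked for arthroplasty and 20 contralateral knees

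Screened knees: 40 + 80 = 120, of 200 in groups A to C.

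**Share of OA-free knees that are screened.** Let q, p and d be the OA-free proportions in screened, operated and Group D contralateral knees. The article gives none of them, so they are assumptions.

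Share = 120q / (120q + 80p + 20d)

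- Groups A to C only, with q at least p: share ≥ 120/200 = 60%.
- With Group D, and q at least as large as both p and d: share ≥ 120/220 = 55%.
- With q = 0.9:

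| p | 0.3 | 0.5 | 0.7 | 0.9 |
|---|---|---|---|---|
| d = 0 | 82% | 73% | 66% | 60% |
| d = 0.5 | 76% | 68% | 62% | 57% |

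The majority is lost only if 120q < 80p + 20d. With d = 0 that means q below 0.67 when every operated knee is OA-free, or q below 0.33 when p = 0.5.

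**Effect on specificity.** Pooled specificity is the weighted mean over the two kinds of OA-free knee. Take q = 0.9, p = 0.5, d = 0, so the weight is 108/148 = 0.73, and assume specificity 0.95 in screened knees:
- 0.80 in operated knees: pooled 0.91
- 0.70 in operated knees: 0.73 × 0.95 + 0.27 × 0.70 = 0.88
- 0.95 in operated knees: pooled 0.95, no distortion

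**Effect on AUC.** For a fixed set of cases, the pooled AUC is likewise a weighted mean. Assume normal scores with equal SD, cases 1.2 SD above screened knees, and operated OA-free knees δ SD above screened knees. AUC against screened knees is Φ(1.2/√2) = 0.802, and against operated knees Φ((1.2 − δ)/√2). Take 105 screened and 48 operated OA-free knees (q = 0.875, p = 0.6), weight 105/153 = 0.69:
- δ = 0: 0.802 in both
- δ = 0.25: operated 0.749, pooled 0.69 × 0.802 + 0.31 × 0.749 = 0.786
- δ = 0.5: operated 0.690, pooled 0.69 × 0.802 + 0.31 × 0.690 = 0.767

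With weight 0.60 and δ = 0.5 the pooled AUC is 0.60 × 0.802 + 0.40 × 0.690 = 0.757.

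**Precision within operated knees** (Hanley-McNeil, AUC 0.75, one knee per person). Q₁ = 0.75/1.25 = 0.600, Q₂ = 2 × 0.5625/1.75 = 0.643.
- 32 OA, 48 OA-free: variance = (0.1875 + 31 × 0.0375 + 47 × 0.0804)/1536 = 0.00334, SE 0.058, 95% interval about ±0.11
- 8 OA, 72 OA-free: variance = (0.1875 + 7 × 0.0375 + 71 × 0.0804)/576 = 0.0107, SE 0.103, about ±0.20

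**The case against.** The other side has several good points.

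- **Intended use.** A reader might infer that the device is meant only for operated knees. The article does not say so. Its Introduction lists ageing, obesity and repetitive stress beside injury as risk factors, and Limitations treats the post-surgical sample as a limit on generalisation. Untouched knees therefore belong in a broader early-detection question.
- **Pooling.** A reader might also take it as stated that the AUC pools all knees. That is inferred from bilateral measurement and the absence of any restriction. A breakdown by knee type could sit in a fuller plan that is not shown.
- **Direction and size.** Both rest on assumed values. With no shift between operated and untouched OA-free knees there is no distortion, and a shift the other way would reverse it. The 50% figure under Project Population is an upper value without a time horizon, whereas these knees are 2 or 5 years after surgery.
- **Design stage.** This is an exploratory pilot. Healthy and late-stage anchors and a screened within-person control are deliberate and useful.
- **Selecting on 80 knees.** Choosing among many candidate parameters on the operated knees alone, with an interval of ±0.11 to ±0.20, would invite selection by noise.

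These points stand. They argue against replacing the all-knee analysis and against calling the bias established. They do not justify reading an all-knee figure as performance in previously injured or operated knees. The Limitations section discusses sample size, generalisation, movement patterns and incomplete surgical history, but not the make-up of the OA-free knees.

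**Conclusion.** The point holds as a limit on what an all-knee AUC or specificity can support. The knee counts follow directly from the plan. That screened knees will form most OA-free knees is a projection, but it needs only that they are OA-free at least as often as operated and Group D contralateral knees. The shares tabulated for q = 0.9 run from 57% to 82%.

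Optimism is the expected direction under the article's own account of joint sound. Its size is unknown: in the illustrations the all-knee AUC exceeds the figure against operated OA-free knees by 0 to about 0.08, and pooled specificity exceeds the operated-knee value by 0 to about 0.18. These show scale and are not estimates. The documents do not support the stronger readings that the reported accuracy will certainly be inflated, or that operated knees are the only valid comparison.

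**What to change.** Keep the all-knee analysis for parameter development, and add:

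1. AUC, sensitivity and specificity within the 80 operated knees of groups B and C, osteoarthritis against none, with intervals. There is one such knee per person, so pairing of knees does not complicate the interval.
2. Specificity shown separately for Group A, comparator and operated knees. This isolates the effect of the OA-free mix, because the operated-knee AUC also changes the cases by leaving out Group D.
3. A check that the parameters selected on all knees still discriminate within the operated knees.
4. A rule that any statement about at-risk post-injury patients or clinical use rests on the operated-knee result with its interval.

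All of this uses data already collected. The cost is a wider interval, about ±0.11 or ±0.20 in the two scenarios above, and possibly a less favourable figure.
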